## Abstract

**Background:**

Patients’ treatment expectations are a key factor in psychotherapy. Several studies have linked higher expectations to better treatment success. Therefore, we want to evaluate the impact of a targeted video-based intervention on patients’ expectations and the treatment success of inpatient rehabilitation.

**Methods/design:**

All patients who will be referred to inpatient psychosomatic rehabilitation in three clinics will receive a study flyer with information about how to log in to the study platform together with the usual clinic information leaflet. Patients will receive the study information and informed consent upon login and will be randomized into the intervention or the control group. The intervention group (*n* = 394) will get access to our virtual online clinic, containing several videos about inpatient rehabilitation, until their admission to inpatient rehabilitation. The control group (*n* = 394) will receive no special treatment preparation. Questionnaires will be given at study inclusion (T0), two weeks before admission to (T1), and at the end of (T2) inpatient rehabilitation. The primary outcome is the outcome expectancy measured with the Credibility Expectancy Questionnaire at T1. Secondary outcomes include treatment motivation, mental health, work ability, depression, anxiety, and satisfaction with and usage of the Internet platform.

**Discussion:**

We expect the intervention group to benefit from the additional preparation concerning their outcome expectancy. If successful, this approach could be used in the future to enhance the efficacy of inpatient rehabilitation.

**Trial registration:**

ClinicalTrials.gov: NCT02532881. Registered on 25 August 2015.

**Electronic supplementary material:**

The online version of this article (doi:10.1186/s13063-016-1417-y) contains supplementary material, which is available to authorized users.

## Background

Patients’ expectations of treatment are considered an important factor in psychotherapy [1]. According to DeFife and Hilsenroth [2], positive expectations are associated with favorable treatment outcome. In his succinct review, Norcross [3] showed that 15 % of the treatment outcome is determined by expectations. Two main types of expectancy are described in the literature [4]. “Outcome expectancy” refers to a person’s beliefs or feelings about a treatment’s efficacy [5]. “Treatment expectancy” refers to a patient’s expectations about how treatment is delivered, e.g., beliefs about the roles in and the duration of therapy [4]. These two types have been validated in several studies [6]. In line with the findings of Norcross [3], Constantino et al. [5] conducted a meta-analysis with 46 studies. They found a small and positive effect, meaning that higher outcome expectations are associated with a more positive outcome, e.g., symptom reduction. This association was found in other studies as well [7, 8].

Constantino et al. [4], as well as Walitzer and Dermen [9], stated that several techniques, like emphasizing the effectiveness of psychotherapy, very likely enhance a patient’s outcome expectancy of psychotherapeutic treatment. Additionally, Kazdin and Krouse [10] found increased outcome expectations when patients received treatment information including successfully treated case examples, technical terms, and information emphasizing the novelty, scientific evidence, and broad focus of the treatment. Furthermore, Constantino et al. [4] concluded that the delivery of a strong treatment rationale has proved to enhance realistic expectations.

Psychosomatic rehabilitation plays an important role in the German inpatient rehabilitation system, which serves to promote and maintain the ability to work of patients with chronic mental diseases. Psychosomatic rehabilitation is one of the main treatment options in Germany for inpatient psychotherapy; there are approximately 200 clinics. About 60 % of mental disorders have a chronic course, often accompanied by impairments at the workplace and deficits in daily functioning [11]. Patients seeking treatment for their mental health problems, however, may not be motivated for the treatment of work-related impairments [12]. Many patients are not well informed about inpatient rehabilitation, and they are thus unaware that the major goal of rehabilitation is to restore their work capacity [13].

Traditionally, patients have been prepared for inpatient rehabilitation by written material, e.g., brochures. Additional preparatory sessions or discussion groups increased acceptance and knowledge and reduced concerns regarding an upcoming rehabilitation. However, they had no significant effect on treatment outcome [14–16]. Zimmer et al. [17] investigated the effect of a multimodal and partly guided online preparation (VORSTAT) for inpatient psychosomatic treatment, including four different modules (social contacts, information, motivation, and support). Similar to the other studies mentioned, the authors found no difference regarding the improvement of health status after the first two weeks of inpatient treatment between the intervention and the control group. The lack of significant findings, though, may be due to the comprehensive control condition. This assumption is supported by a subsequent study [18]. In a naturalistic observational study, the preparation proved to be effective regarding higher rates of reliable improvement of physical and psychological impairments and social problems in the intervention group compared to a non-randomized control group.

It has been shown that the use of videos as an information source for psycho-oncological patients reduced the fear of cancer treatment and increased satisfaction with the clinic allocation [19, 20]. Several studies have demonstrated that personal cancer stories have a positive influence on the health of recipients [21]. Another study indicated that video information led to reduced anxiety in patients with prostate cancer and increased understanding of their disease and its management [22]. Furthermore, Walthouwer et al. [23] showed that videos are more appreciated, emotionally appealing, and attention-getting than written information.

With the studies of Walitzer and Dermen [9], Kazdin and Krouse [10], and Constantino et al. [4] in mind, we assume that preparing patients for inpatient treatment with a targeted video-based intervention will increase their outcome expectancy and induce more realistic expectations. Furthermore, following up on the promising results of Zimmer et al. [18], we will investigate the influence of our preparation on treatment outcome at the end of inpatient rehabilitation as well. Therefore, this study evaluates a targeted intervention using videos of patients performed by actors and videos of experts to prepare patients for psychosomatic inpatient rehabilitation.

## Methods/design

### Participants

All patients referred to inpatient rehabilitation in one of the three cooperating clinics who are more than 18 years old are eligible for study participation. They will receive the study information together with the usual clinic documents and information about inpatient rehabilitation. Together with the study information, each patient will additionally receive a personal code and a link to the Internet platform (IP). After logging into the IP, patients need to agree to the informed consent presented on the platform. Patients who give their informed consent will be randomized to the intervention or control group and will receive the first questionnaire immediately.

Furthermore, all patients who complete all three questionnaires are eligible to take part in a drawing after completing the third assessment. Patients participating in the drawing can win one of ten cash checks worth 50 € each.

Personal data will be stored at the Study Center of Mental Disorders at the University Medical Center of the Johannes Gutenberg-University Mainz and each cooperating clinic. However, the study assistants with access to the personal data will have no access to the research data collected using questionnaires. Administration of the IP will be managed only by research fellows of the Department of Psychosomatic Medicine and Psychotherapy of the University Medical Center Mainz and the study assistants in the cooperating clinics.

The clinical protocol and informed consent were approved by the Ethics Committee of the Federal State of Rhineland-Palatinate (Germany), which is responsible for the coordinating center in Mainz (Ref. Number 837.192.15 (9960)). Additional approval from Ethics Committees responsible for the cooperating clinics is not necessary if the documents submitted by the coordinating center have been approved by an Ethics Committee. All procedures described in the clinical trial protocol (ClinicalTrials.gov identifier: NCT02532881) follow the International Conference on Harmonization-Good Clinical Practice (ICH-GCP) guidelines and the ethical principles described in the current revision of the Declaration of Helsinki. The trial will be carried out in accordance with local legal and regulatory requirements. A SPIRIT checklist is provided as an additional file (see Additional file 1).

Data privacy and data security of the IP are ensured by several means. First of all, access to the platform is Secure Sockets Layer (SSL)-encrypted. Moreover, the patients do not use their real names to access the platform, which means that their real identity cannot be inferred from the data collected over the platform. Finally, the IP is located on a firewall-protected Web server. As no personal data are stored on the Web server, identification of the user’s identity is not possible.

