The second set of videos consists of explanatory videos with explicit explanations of concepts, terms, therapies, and other relevant aspects of rehabilitation. This information is presented by fictional experts from different occupation groups working in inpatient rehabilitation. The roles of the experts are performed by actors and staff from the study center on the basis of the scripts previously created by the psychologists of the study center. All topics included in the scripts have been reviewed and revised by corresponding experts in two cooperating clinics and the German Statutory Pension Insurance.

The user can freely choose the videos of both sets. Participants of the intervention group will get access to the IP after they have given their informed consent. Access will expire when subjects are admitted to inpatient rehabilitation.

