### Control condition

The control group receives no intervention in addition to the usual inpatient rehabilitation preparation (“as usual”). The preparation contains written information about inpatient psychosomatic rehabilitation and a link to the homepage of the respective clinic.

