### Assessment

Assessments will be conducted at study inclusion (T0), two weeks before admission to (T1), and at the end of inpatient rehabilitation (T2; see Fig. 1). Questionnaires at T0 and T1 will be given online. At T2 questionnaires can also be administered in paper and pencil form. At T0 patient characteristics like family status and employment will be assessed together with the patient’s history of pre-treatment. Their Internet use will be ascertained as well. The following instruments are used at each time point. The short form of the Patient Health Questionnaire-4 (PHQ-4) [25] will be used to measure depression and anxiety. The mental condition will be assessed at each time point with the Indicators of Rehabilitation Status (IRES-24) [26]. Additionally, patients’ ability to work will be assessed with the Subjective Prognosis of Work Capacity (SPE) [27]. To measure the patient’s expectancies, the Credibility Expectancy Questionnaire (CEQ) [28] will be given at T0 and T1. Furthermore, the Work-Related Therapy Motivation Questionnaire (FBTM) [29], the Questionnaire for Assessment of Rehabilitation Expectancy and Motivation (FREM-17 [30]), and the Patient Questionnaire for Assessment of Rehabilitation Motivation-20 (PAREMO-20 [31]) will be used to assess work-related therapy motivation and treatment motivation at T0 and T1 as well. The use of the IP and websites with clinic reviews and ratings as well as the clinic websites will be measured only at T1. Patients will be asked about their satisfaction with inpatient treatment at T2. All questionnaires and the time points at which they are administered are displayed in Table 1.

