**Fig. 1 Fig1:**
[figure not shown]
Study design and time points of assessment. *IG* intervention group, *CG* control group, *TAU* treatment as usual

**Table 1 Tab1:** Schematic overview of frequency and scope of the study visits

Visits/scope	First login on platform	After randomization	Before inpatient rehabilitation	End of rehabilitation
Study visits		T0	T1	T2
Written informed consent	X			
Internet use		X		
Pre-treatment		X		
CEQ		X	X	
FBTM		X	X	
FREM-17		X	X	
PAREMO-20		X	X	
PHQ-4		X	X	X
IRES-24		X	X	X
SPE		X	X	X
IP usage			X	
Use of websites with clinic reviews and clinic website			X	
BADO			X	X
Patient Satisfaction Questionnaire-8 (ZUF-8)				X

*BADO* Basis documentation

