### Outcomes

The primary outcome in the study is the outcome expectancy (CEQ) measured at T1 (two weeks before admission to inpatient rehabilitation).

Key secondary outcomes are:Work-related therapy motivation (FBTM) at T1Treatment motivation (FREM-17 and PAREMO) at T1Treatment credibility (CEQ) at T1Satisfaction with and usage of IP at T1Mental condition (IRES-24) at T2 (end of rehabilitation)Satisfaction with inpatient rehabilitation (ZUF-8) at T2Subjective prognosis of work ability (SPE) at T2Depression and anxiety (PHQ-4) at T2Functioning in everyday life (IRES-24) at T2Perceived advantage of aftercare at T1 and T2

Predictors of outcome are:Therapy motivation (FREM-17 and PAREMO-20) at T0 (after randomization)Internet use and technology affinity at T0Use of websites with clinic reviews and ratings as well as use of the cooperating clinics’ websites at T1Previous, especially rehabilitation, treatments prior to the current inpatient rehabilitation at T0

We have defined four predictors of outcome which may have an additional impact on outcome, potentially confounding the impact of patients’ expectations. As it has a major influence on the therapy success, treatment motivation will be controlled [32]. We further think that strong Internet use and technology affinity may influence the use of our platform [33]. We will control for the use of websites with clinic reviews and ratings as well as the use of the cooperating clinics’ websites. Finally, we need to know if patients have had prior inpatient (rehabilitative) treatments, as previous experience may influence expectations. All predictors will be used as control variables in additional explorative analyses after testing our primary and secondary outcomes.

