### Sample size calculation

Effect sizes will be calculated to describe treatment effects. We anticipate small effects (*d* = .24) concerning the primary outcome [4]. Based on a level of significance of *p* < .05, a statistical power of .80, one covariate, and two groups, *N* = 788 patients (394 in the control group and 394 in the intervention group) are necessary to detect a between-group effect (a priori power analysis of an ANCOVA with GPower version 3.1). With an expected participation rate of 32 % [34], we need to ask *N* = 2459 patients for study participation to reach this sample size. Considering that there were 4496 patients in the three cooperating clinics per year, we need to recruit patients for at least seven months to reach the planned sample size.

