### Statistical methods

Analysis of covariance will be used to evaluate the CEQ scores at T1 between the intervention and control groups with CEQ score at T0 as the covariate. The first eight secondary outcomes will be analyzed with analyses of covariance in analogy to the primary outcome. The last two secondary outcomes will be reported with descriptive statistics. Intention-to-treat analyses with multiple imputations to replace missing data as well as per-protocol analyses will be conducted.

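### The T0 CEQ, covariate of the primary ANCOVA, is collected after randomization with no stated safeguard; if allocation or early access moves it, the primary estimate shrinks toward the null

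*Protocol article*

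**What the plan says.** Three places in the protocol article put T0 after randomization.

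- Participants: "Patients who give their informed consent will be randomized to the intervention or control group and will receive the first questionnaire immediately".
- Table 1: the column that holds study visit T0, with the CEQ marked in it, is headed "After randomization".
- Outcomes, list of predictors: "Therapy motivation (FREM-17 and PAREMO-20) at T0 (after randomization").

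On access, the Intervention section says: "Participants of the intervention group will get access to the IP after they have given their informed consent". Completion of T0 is not given as a condition. Under Control condition, "The control group receives no intervention in addition to the usual inpatient rehabilitation preparation".

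On analysis, the Assessment section says "the Credibility Expectancy Questionnaire (CEQ) [28] will be given at T0 and T1", and Statistical methods compares T1 CEQ between arms "with CEQ score at T0 as the covariate". The first eight secondary outcomes are to be analysed by ANCOVA on the same pattern. Intention-to-treat analyses with multiple imputation are planned alongside per-protocol analyses.

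**The concern.** Covariate adjustment in a randomized trial is safe when allocation cannot have affected the covariate. Measurement before randomization guarantees this. Measurement afterwards does not, unless patients are still unaware of their arm and have had no contact with the intervention.

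The covariate and the primary endpoint here are the same self-rated expectancy instrument, and the intervention is designed to raise expectancy. Being offered the virtual clinic, or finding that one will not get it, could move the score before any video is watched. The article describes no masking of patients and no step that withholds allocation or access until T0 is submitted.

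At stake is mainly the primary estimate: adjusting for a T0 difference that allocation caused subtracts part of the effect. Secondary ANCOVAs share the problem where their own T0 score could be moved in the same way, mainly FBTM, FREM-17, PAREMO-20 and CEQ credibility. In addition, a patient who leaves between randomization and T0 contributes no T0 data, not even patient characteristics, to the imputation.

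**Working it through.** **The plan's own figure.** Sample size calculation states d = .24, alpha .05, power .80, one covariate, two groups and N = 788. With noncentral F power (f = d/2, lambda = N·f², df = 1 and N − 3), d = .24 needs N = 547, so 788 is not reproduced. N = 788 corresponds to d = .20 (N = 787, or 394 per arm after rounding up). At d = .24, N = 788 gives power .92. That mismatch is a separate matter; here it only sets the starting points .92 (d = .24) and .80 (d = .20).

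**The mechanism.** Let D1 be the T1 difference between arms, D0 the T0 difference caused by allocation or early access, and b the within-arm slope of T1 on T0.

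- Expected ANCOVA estimate = D1 − b·D0.
- With equal SDs at T0 and T1, b equals the T0–T1 correlation r. Writing D0 = s·D1, where s is the share of the T1 effect already present at T0, the estimate is D1·(1 − r·s).
- The proportional loss is r·s. It is zero if s = 0 or r = 0.

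A positive D0 arises if intervention patients' T0 rises or controls' T0 falls; either one pulls the estimate toward the null.

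**Inputs.** d = .24 and N = 788 come from Sample size calculation. The article gives neither r nor s, so both are assumptions shown over a range.

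**Results** for d = .24 on the residual-SD scale, N = 788 (loss; power):

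| s | r = .3 | r = .5 | r = .7 |
|---|---|---|---|
| 0 | 0%; .92 | 0%; .92 | 0%; .92 |
| .10 | 3%; .90 | 5%; .89 | 7%; .88 |
| .25 | 7.5%; .875 | 12.5%; .84 | 17.5%; .79 |
| .50 | 15%; .82 | 25%; .71 | 35%; .59 |

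Worked cells at r = .5:

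- s = .10: .24 × (1 − .05) = .228, power .89.
- s = .25: .24 × (1 − .125) = .210, power .84.

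A simulation of the second case (394 per arm, 4,000 runs) gave a mean estimate of .212 against .210 expected.

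**Sensitivity to the starting point.**

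- If the effect is d = .20, the value that N = 788 matches, r = .5 gives .190 and power .76 at s = .10, and .175 and power .69 at s = .25.
- If d = .24 is in raw-SD units, the effect is divided by √(1 − r²) = .866 before the F test. Power at r = .5 is then .97 with no shift, .96 at s = .10 and .93 at s = .25. The percentage loss is unchanged.

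**Which secondary outcomes.** In Table 1, FBTM, FREM-17, PAREMO-20 and the CEQ are given at T0 and T1. PHQ-4, IRES-24 and SPE also have T0 scores, but they measure symptoms, functioning and work prognosis, and the article gives no reason why learning one's arm would move these at once. ZUF-8 (T2 only) and platform usage (T1 only) have no T0 score.

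**The case against.** The strongest reply is that the harm needs a fact the article does not state. Randomization carried out silently by the platform's algorithm cannot change a T0 answer; patients must first learn their arm or open the videos. No section says when allocation is shown. The one statement on sequence has the questionnaire follow at once, which argues against prior viewing. The access sentence says who gets access and from what event; it does not place access before T0. Screen-by-screen gating is also detail that an article may leave to the full protocol. All of this stands, and it is why the size has to include zero. It does not remove the point: the article itself fixes T0 after randomization in three places and fixes T0 CEQ as the primary covariate, and it states nothing that protects that covariate.

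Several stronger readings are tempting but unsupported.

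- **That patients do see their arm or the videos before T0, or that controls drop out on learning theirs.** The article leaves this open.
- **That every secondary ANCOVA is biased.** ZUF-8 and platform usage have no T0 score to be affected.
- **That the intention-to-treat analysis is broken.** Randomized patients stay in the set and multiple imputation is planned. What is lost is T0 information on those who leave early.
- **That a shift of .10 or .15 SD should be expected.** Those would be 42% and 63% of the anticipated effect (.10/.24 and .15/.24), arising before a questionnaire handed out at once. Nothing in the article supports shifts of that size.
- **That false positives increase.** If allocation affects neither T0 nor T1, type I error is not inflated. In the direction described here the bias hides a benefit, so a positive primary result would survive it.

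**Conclusion.** The concern holds in conditional form. The covariate of the primary ANCOVA is a post-randomization measurement of the same construct as the endpoint, and the article states no safeguard. If allocation or early access moves T0 expectancy in the intervention arm's favour, the primary estimate is too small by slope times the T0 difference, and the motivation and credibility ANCOVAs are exposed in the same way.

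The size is not known from the article. With an assumed T0–T1 correlation of .5, equal SDs at the two visits and d = .24 on the residual-SD scale, the loss runs from 0% with no shift, through 5% with a tenth of the effect present at T0, to 12.5% with a quarter present. Power at N = 788 is then .92, .89 and .84. It stays above the planned .80 in these cases, but not if the effect is nearer the .20 that N = 788 matches. The issue merits correction because the remedy is cheap, and because once data are collected a T0 difference caused by allocation cannot be told apart from chance imbalance.

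**What to change.** Reorder the platform: consent, complete T0, randomize, reveal allocation, open access. Relabel T0 in Table 1 and in the Outcomes section as before randomization, and tie platform access in the Intervention section to completion of T0. If the order cannot be changed, state and implement the minimum safeguard: allocation hidden and videos locked until T0 is submitted. Should the platform already work this way, a sentence saying so settles the matter of the covariate.

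For anyone enrolled under the current order:

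- report T0 CEQ by arm, with the number randomized but without T0 in each arm;
- use the platform's tracking data, described in the Discussion, to show whether videos were opened before T0;
- add a sensitivity comparison of T1 CEQ adjusted for clinic only.

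Cost: a workflow change and a short amendment. Both randomization and the T0 questionnaire already run on the platform. Patients who consent but do not finish T0 would no longer be randomized, so the yield per invitation falls slightly. The sensitivity analysis gives up the precision that the covariate brings: with d = .24 in raw-SD units, r = .5 and no T0 shift, power at N = 788 goes from .97 with the covariate to .92 without it (clinic adjustment ignored).
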